#### Recruitment

The recruitment of participants will be conducted by a study coordinator who is employed by the rehabilitation center. This study coordinator will screen all persons undergoing rehabilitation, who start their medical rehabilitation program during either the preparation phase (i.e., CG) or maintenance phase (i.e., IG), for their eligibility.

#### Blinding

As all participants will receive both verbal and written information about the study as the legal basis for their informed consent to participate, they will be aware of the scientific purpose of evaluating exercise and physical therapy in medical rehabilitation. However, concealment can be ensured as to whether participants are part of the IG or CG. In contrast, exercise and physical therapists, as providers of the intervention, will be fully aware of the study procedure, meaning that no blinding can be realized at the facilitator level.

#### Data collection

To evaluate the effectiveness of the modified exercise and physical therapy in the short- and long-term, outcomes will be assessed at the beginning of medical rehabilitation (T0), at the end of medical rehabilitation (T1), and one year after the beginning of medical rehabilitation (T2) (see Fig. 2). We will collect participants’ data on PAHCO, PA, general health and basic socio-demographic information via a paper-pencil questionnaire. The disease-specific information will be obtained via a medical form, which will be used as part of routine diagnostics at the participating rehabilitation centers, and the therapy-specific information will be gathered via a documentation form, which will be completed by the study coordinator. The study coordinator located at each rehabilitation center will administer the data collection procedure by handing out the questionnaires at the beginning (T0) and end (T1) of medical rehabilitation and sending them via postal mail at the 1-year follow up (T2).

#### Data management

In addition to the self-reported data of the persons undergoing rehabilitation, the study coordinator will digitalize the disease-specific information from the medical form. A continuous pseudonym will link all the data sources of the participants across the time points. The storage and processing of the data collected will be performed in SPSS (IBM, Armonk, USA).

#### Data analysis

The data set for persons undergoing rehabilitation will contain longitudinal data at the individual level. Specifiable as within-subjects factors, calculations can encompass comparisons between the beginning (T0) and the end of medical rehabilitation (T1) as short-term effects and respective comparisons with data at one year after starting medical rehabilitation (T2) as follow-up effects. In addition, the data set will contain longitudinal data on the level of the rehabilitation center (i.e., prior to the development of modifications, representing the CG, and after the implementation of the modified exercise and physical therapy, representing the IG; between-subjects factor). Since the effectiveness may vary among the three rehabilitation centers, we consider the setting as a control variate. We will integrate all these factors into repeated MANCOVA with the primary outcomes. To counteract outlier problems with the PA outcome, we will apply the winsorization technique to cut all values beyond the 95th percentile [53]. We will subsequently use the indicated frequencies and mean durations to calculate a corresponding total index in addition to a separate sport activity index. Calculations with the secondary outcomes will be treated as exploratory analyses. Nevertheless, we will adopt an intention-to-treat paradigm, meaning that all persons undergoing rehabilitation meeting the eligibility criteria and initially providing consent will be included in the statistical effectiveness computations. Reasonable dropouts (e.g., discontinuation of the planned medical rehabilitation program) will be treated as structurally missing data, whereas other missing items and measurements will be imputed with the expectation maximization algorithm [54]. We will run the analyses with the open source R (version 4.3.1 or higher) and interpret effect sizes (*η*²) according to the guidelines by Cohen [55], providing benchmarks to define small (*η*^2^ = 0.01), medium (*η*^2^ = 0.06), and large (*η*^2^ = 0.14) effects.

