### Study design and setting

We will simultaneously evaluate the effectiveness and implementation of modified exercise and physical therapy within a multicenter non-randomized controlled trial. The study will take place in three inpatient rehabilitation centers in Bavaria, Germany, between September 2023 and May 2027. These rehabilitation centers are part of the clinic association of the German Pension Insurance (Ger.: Deutsche Rentenversicherung) in Bavaria, Germany, with a specialization in indications in the fields of orthopedics, rheumatology and/or internal medicine. According to the tenth revision of the International Statistical Classification of Diseases and Related Health Problems (ICD-10) [39], examples of health conditions treated in these clinics include type 2 diabetes mellitus (E11), obesity (E66), coxarthrosis (M16), gonarthrosis (M17), cervical disc disorders (M50) other intervertebral disc disorders (M51), other dorsopathies (M53), dorsalgia (M54), and shoulder lesions (M75). The rehabilitation centers confirmed their willingness to participate in this study in a letter of intent. The corresponding costs for the personnel resources required to complete the study are included in the funding requested and are provided to the rehabilitation centers.

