### Effectiveness study

To determine the short- and long-term effectiveness of modified exercise and physical therapy on PAHCO and PA in persons undergoing rehabilitation, these effects will be compared with those of exercise and physical therapy conducted before modification (see Fig. 2). Owing to the prevailing organizational characteristics in the real-world setting, we will pursue a pragmatic evaluation approach based on a quasi-experimental design [46]. For this purpose, individuals undergoing inpatient medical rehabilitation will be recruited at two different time periods, namely, (a) prior to the development of modifications in the preparation phase, representing the control group (CG) receiving usual exercise and physical therapy, and (b) after the implementation of the modified exercise and physical therapy in the maintenance phase, representing the intervention group (IG) receiving modified exercise and physical therapy. In this context, we hypothesize that the changes in PAHCO and PA in persons undergoing rehabilitation after the modification of exercise and physical therapy (i.e., IG) will be significantly higher than the changes in PAHCO and PA in persons undergoing rehabilitation before the modification of exercise and physical therapy (i.e., CG).

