**Further participant data**				
Basic sociodemographic data	Questionnaire on age, height, weight, sex, work ability, employment status, education	X		
Disease-specific information^1^	Medical form stating indication/diagnosis, disease severity/degree of disability, comorbidities	X		
Therapy-specific information^1^	Documentation form stating duration and content of exercise and physical therapy		X	

Note: ^1^We cannot assume uniform assessments for these data, as the assessments may vary between the rehabilitation centers, for example due to different standard diagnostics or therapy documentation

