Although the present study may add value to PAP within medical rehabilitation, we consider the following limitations. First, all rehabilitation centers are longitudinally compared against their previous concept (i.e., intra-organizational control with intervention and control periods). Against this background, we cannot fully exclude that cohort or historical effects over time (e.g., reforms of the entire rehabilitation system, severe disease waves, labor disputes of therapist associations) may affect the results, which cannot be methodologically controlled by this study design. In any case, we will closely follow relevant processes within the rehabilitation centers (e.g., other interventions being conducted in parallel with our study) as well as the political atmosphere, health-related debates, and upcoming guidelines relevant for the German rehabilitation system (e.g., via the expert panel) to provide potential explanations for the final interpretation of the results. Furthermore, the study procedure causes a 16-month time gap between the measurement time points of the CG and the IG, so that potential seasonal effects cannot be eliminated. However, the seasonal effects across the three rehabilitation centers are not systematically distributed for either the IG or the CG because of the sequential design and the associated measurement time points. Second, to the best of our knowledge, this study is the first to apply a co-creation approach to modify exercise and physical therapy in medical rehabilitation, with the aim of promoting long-term PA among persons undergoing rehabilitation in Germany. Owing to the complex approach to modifying the therapy concept, the study can only include three rehabilitation centers. Accordingly, we can only treat the rehabilitation centers as covariates instead of systematically considering the cluster effect through multilevel modeling (for sample requirements, see [58]).

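### The primary before/after comparison adjusts only for centre, although prognostic patient data are collected at T0, so a case-mix shift between the cohorts can bias the group-by-time effect

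*Protocol article*

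**What the plan says.** Study design and setting calls the study a "multicenter non-randomized controlled trial". The Effectiveness study section explains that "individuals undergoing inpatient medical rehabilitation will be recruited at two different time periods": the CG in each centre's preparation phase and the IG in its maintenance phase. The hypothesis concerns change, with a larger change expected in the IG.

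The Data analysis section for the effectiveness study lists the model terms. Time (T0, T1, T2) is the within-subjects factor and CG versus IG the between-subjects factor. On centre it says "Since the effectiveness may vary among the three rehabilitation centers, we consider the setting as a control variate". It then concludes: "We will integrate all these factors into repeated MANCOVA with the primary outcomes". The limitations paragraph of the Discussion again names only the centres as covariates.

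Table 2 shows what else is available at T0:
- sociodemographic data: "Questionnaire on age, height, weight, sex, work ability, employment status, education";
- disease data: "Medical form stating indication/diagnosis, disease severity/degree of disability, comorbidities", with a note that "We cannot assume uniform assessments for these data, as the assessments may vary between the rehabilitation centers";
- the BSA activity questionnaire and the IRES-24 health questionnaire, as baseline values of the secondary outcomes.

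The effectiveness model gives none of these a role as a covariate, and no weighting or matching is named.

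On season, the Discussion first concedes that the 16-month gap leaves seasonal effects in place. It then says that "the seasonal effects across the three rehabilitation centers are not systematically distributed for either the IG or the CG".

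**The concern.** In a non-randomised comparison of two period cohorts, nothing in the design balances the patients. Eligibility is broad: any inpatient with sufficient German who consents, in centres that treat conditions from obesity and type 2 diabetes to joint and back disorders. If referral patterns or the indication mix drift over 16 months, the two cohorts may differ in characteristics that predict how much a patient's competence scores change.

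Repeated measurement does not deal with this. Subtracting T0 cancels a constant difference in level. It does not cancel a difference in expected change by diagnosis, age or starting activity, nor regression to the mean from different starting points. Such a difference goes into the group-by-time term, which is the estimate of the intervention effect. The protocol collects the data that would address the measured part of the problem but fixes a primary model that does not use them.

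**Working it through.** **1. The protocol's own figure.** Inputs from Sample size: f = 0.20, alpha 0.05, power at least 80%, N = 244. The formula is not stated. A group-by-time F test with two groups and three time points reproduces the figure: df1 = 2, df2 = N − 3 = 241, noncentrality = f² × N = 0.04 × 244 = 9.76, power 0.8002. The stated correlation r = 0.40 does not enter this variant.

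**2. How much an unadjusted shift could matter (assumed inputs).** Take one outcome and one change score, 244/2 = 122 per group, r = 0.40, and the outcome SD as unit.
- Variance of change = 2(1 − 0.40) = 1.2.
- SE of the group difference = √(1.2 × 2/122) = 0.140.
- Type I error under bias b = 1 − Φ(1.96 − b/SE) + Φ(−1.96 − b/SE).

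| Bias b (SD) | One way it could arise (assumed) | True type I error |
|---|---|---|
| 0.03 | subgroup changing by 0.3 SD more, its share shifts 10 points | 5.5% |
| 0.05 | subgroup changing by 0.5 SD more, its share shifts 10 points | 6.5% |
| 0.09 | change rises 0.3 SD per SD of a factor that shifts 0.3 SD | 9.8% |
| 0.15 | subgroup changing by 1.0 SD more, its share shifts 15 points | 18.8% |

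The shift here means a systematic difference between the two source populations. Chance imbalance is already reflected in the standard error.

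**3. What adjustment costs.** Same F test as in step 1.
- Degrees of freedom only: with 14 extra, df2 = 227 and power is 0.7999 instead of 0.8002.
- If covariates explain an assumed 5%, 10% or 20% of residual variance (noncentrality divided by 1 − R²), power is 0.82, 0.84 or 0.88.
- If covariates instead share an assumed 5%, 10% or 20% of variance with period (noncentrality multiplied by 1 − R²), power is 0.78, 0.75 or 0.70.

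**4. The season sentence.** The gap is 16 = 12 + 4 months, so in every centre the IG falls four calendar months later in the year than the CG. The stagger between centres is 5 months (Study procedure). Assume that centre 1 starts in September 2023 and that recruitment fills four-month windows from the start of each phase. CG windows then begin in September, February and July, and IG windows in January, June and November.
- For a yearly cosine, the mean vector of starts at 0°, 150° and 300° has length 0.244.
- A four-month shift is 120°, so the CG–IG difference is at most 0.244 × 2 sin 60° = 0.42 of the amplitude using start months, or 0.35 after averaging over the windows.

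The stagger therefore dampens an annual cycle but does not remove it. This applies to levels. T1 usually follows T0 by about three weeks and T2 follows by one year, so an additive season effect largely cancels in change from T0, most clearly for T0–T2.

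**The case against.** The strongest case against runs as follows.

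- *A covariate list can be completed in an analysis plan, and naming these factors does not exclude others.* This has some force. But the article does not leave the model open. It lists the factors and describes centre as the control variable, and the Discussion again mentions only centres. Followed as written, the analysis makes no case-mix adjustment.
- *Both cohorts come from the same three centres under the same criteria, with all starters screened, so the shift may be small.* This stands. The documents give no estimate of drift, and at 0.03 to 0.05 SD the inflation is only to about 5.5% to 6.5%. The illustration is also a single univariate contrast, and the error rate of the planned three-outcome test was not computed.
- *Adjustment can cost precision and is not the only remedy.* This also stands. Overlap with period costs power, and weighting would be an alternative.

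A reader might go further and infer that season shifts count as intervention effect and that admission date is at hand to correct them. The documents do not support that. Admission date is not among the listed data, and within a centre the CG and IG windows do not overlap, so calendar date is largely confounded with period. Additive season effects largely cancel in change from T0, and the Discussion already discloses that season remains.

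A reader might also take the Discussion's remark that cohort or historical effects cannot be controlled as a wrong claim about case mix. Its examples are external events (system reforms, disease waves, labour disputes), and for those it is right. It does not address measured patient characteristics.

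**Conclusion.** The point holds for measured case mix. The stated primary model has time, period and centre only, in a non-randomised comparison of different patients, while plausible prognostic T0 data go unused. The group-by-time effect is therefore open to bias wherever the two cohorts differ in characteristics that govern the amount of change.

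The size cannot be known from the documents. The range of about 5.5% to 19% for a nominal 5% test rests on assumed biases of 0.03 to 0.15 SD, 122 per group and r = 0.40.

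It does not follow that the comparison is invalid, or that adjustment would make a significant result attributable to the modified therapy. Unmeasured differences and history remain confounded with period either way, as the protocol acknowledges for history. The season sentence is a secondary matter of wording: a uniform four-month shift within every centre does not fit well with a claim of no systematic distribution.

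**What to change.** In the Data analysis section, prespecify a short set of T0 covariates in the primary model, each with its time interaction: age, sex, BMI (from height and weight), education, employment status, ICD-10 indication group, T0 BSA activity and T0 IRES-24. Use indication group rather than severity, because the note to Table 2 warns that disease assessments may differ between centres. Report the centre-only model as a sensitivity analysis. Fixing the list now also prevents covariates from being chosen after the data are seen.

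In the Discussion, soften the season sentence: say that the IG falls four calendar months later than the CG in each centre and that the stagger dampens this only partly. Any seasonal term belongs in a sensitivity analysis, and only if admission dates are recorded.

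The cost is wording and few degrees of freedom: about 12 if education and employment take two each and indication three (assumed), which is within the 14 checked above. Precision may improve if the covariates are prognostic. If they overlap with period, power falls to about 0.78 to 0.70 for an assumed 5% to 20% shared variance.

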#### Eligibility criteria

For inclusion in the study, the persons undergoing rehabilitation must fulfill the following eligibility criteria: (A) participation in an inpatient medical rehabilitation program at the respective time period (i.e., preparation phase for CG or maintenance phase for IG), (B) sufficient ability to read, comprehend, and write in the German language, and (C) provision of written informed consent to participate in the study. Accordingly, all participants who (A) discontinue the planned medical rehabilitation program, (B) have an insufficient ability to read, comprehend, and write in the German language, or (C) withdraw their original consent for participation are excluded.

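### The effectiveness analysis is labelled intention-to-treat, yet participants who discontinue rehabilitation are excluded after enrolment and left out of the imputation, so the primary analysis set depends on a post-exposure event

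*Protocol article*

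**What the plan says.** All statements are in the effectiveness study part of the protocol article.

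- **Data analysis, analysis set.** After naming an intention-to-treat paradigm, the text says that "all persons undergoing rehabilitation meeting the eligibility criteria and initially providing consent will be included in the statistical effectiveness computations".
- **Eligibility criteria, exclusions.** The list covers "all participants who (A) discontinue the planned medical rehabilitation program", people with insufficient German, and those who "withdraw their original consent for participation are excluded". The language criterion can be checked at entry. The other two can occur only after the person has joined.
- **Data analysis, missing data.** The rule for people who leave early reads: "Reasonable dropouts (e.g., discontinuation of the planned medical rehabilitation program) will be treated as structurally missing data". The same sentence contrasts them with all remaining gaps in the data, which are filled by expectation-maximization imputation.
- **Data analysis, model.** "We will integrate all these factors into repeated MANCOVA with the primary outcomes", with time as the within-subjects factor, period (control or intervention group) as the between-subjects factor, and centre as a control variate.
- **Data collection.** T1 is handed out in the centre at the end of rehabilitation. T2 is posted one year after the start of rehabilitation.

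**The concern.** An intention-to-treat set is fixed at entry and does not depend on what happens afterwards. Here, two events after entry decide who counts. The more important is discontinuation of the programme: it follows exposure to the therapy being evaluated, so the therapy may influence it.

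The control and intervention groups are also recruited in different, non-randomized periods. If the modified therapy, or anything else that differs between periods, changes who stays to the end, the comparison is between two differently selected groups. The Discussion acknowledges cohort, historical and seasonal effects, but not this further selection after exposure.

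At stake are who enters the primary analysis and whether a published result may be called intention-to-treat.

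**Working it through.** **1. One participant followed through the text.** Take a person who meets the entry criteria, consents, completes T0 and discontinues rehabilitation before T1.

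| Statement | What happens to this person |
|---|---|
| Analysis-set sentence, read by initial consent | Included |
| Exclusion criterion (A) | Excluded |
| Missing-data sentence | Apparently still in the data set, but set apart from the imputed values |

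Two readings are possible.

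- *Reading 1.* The analysis-set sentence requires that the eligibility criteria be met, so it takes in exclusion (A). The person leaves the set. The sections are then consistent on who is analysed, but the set is not intention-to-treat.
- *Reading 2.* Initial consent is enough and the person stays in. That contradicts exclusion (A). With T1 missing and not imputed, the person still supplies no T0-to-T1 change to a repeated MANCOVA, which needs the repeated measurements. The protocol does not say that the model drops such cases; this is an inference from the planned method.

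Under both readings the discontinuer contributes nothing to the estimated change.

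**2. Who is retained.** Someone who finishes rehabilitation but skips items, or does not return T2, falls under the expectation-maximization rule and stays in. The condition is completion of rehabilitation, not completeness of data.

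**3. Number of people the plan allows for (Sample size section).** The plan needs 244 in total: 82 per centre, 41 per period and centre. With 15% dropout it recruits 48 per period and centre.

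- Recruited: 3 × 2 × 48 = 288.
- Remaining after 15%: 288 × 0.85 = 244.8, which matches the required 244.
- Allowance for losses: 288 − 244.8 = 43.2, about 43 people.

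The 15% is described as longitudinal dropout. It is not split into discontinuation, consent withdrawal and non-return of T2, so the number who would leave the analysis set is unknown.

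**4. Form of the bias.** In group g, let p_g be the discontinuation rate, and let G_g be the mean change in completers minus the mean change in discontinuers.

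- Full-group mean = completer mean − p_g × G_g.
- Bias in the IG − CG contrast = p_IG × G_IG − p_CG × G_CG.
- With a common gap G: bias = (p_IG − p_CG) × G.

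The documents give neither p nor G for either group. As an illustration under assumed values only, rate differences of 5 and 10 percentage points and gaps of 0.5 and 1.0 SD give:

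- 0.05 × 0.5 = 0.025 SD
- 0.05 × 1.0 = 0.05 SD
- 0.10 × 0.5 = 0.05 SD
- 0.10 × 1.0 = 0.10 SD

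The sign depends on which group loses more people and on the sign of G. The documents settle neither.

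**The case against.** **Much of the sample is protected.** A reader might infer a plain completers' or complete-case analysis under an intention-to-treat label. The text does not support that: missing items and measurements of people who finish rehabilitation are imputed. This stands, and the point is limited to discontinuers and, through the exclusion list, consent withdrawals.

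**Consent withdrawal is a smaller matter.** Ceasing to collect data after withdrawal is normal. What remains is narrow: analysing everyone who initially consented conflicts with excluding the person altogether, including data already given.

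**The size is not established.** A reader might express the illustrative bias as a share of the planned effect by converting f = 0.20 to d = 2f = 0.40. That conversion holds for a two-group contrast with 1 degree of freedom. The stated 244 is reproduced by an F test with 2 numerator degrees of freedom, whereas 1 degree of freedom gives 199. So d = 0.40 is not a planning value of this protocol. A 10-point difference in discontinuation also means at least 5% discontinuing on average across two equal groups, within a stay of usually three weeks; that is an upper-end scenario. Nor is there support for saying which group would be favoured.

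**There is no randomization to protect.** This is true, and confounding by period remains whatever is done here. It does not make it harmless to select again after exposure, nor does it make the label correct.

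**An unseen analysis plan may define structurally missing.** It may, and the missing definition is not held against the article. The conflict between the intention-to-treat statement and the exclusion list is in the published text itself.

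**Conclusion.** The point holds in this limited form. As written, the primary analysis excludes people on the basis of discontinuing rehabilitation, an event after exposure whose frequency may differ between the control and intervention periods. It is not intention-to-treat, even though people who complete rehabilitation and have other gaps are retained by imputation.

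This rests on the wording of the two sections and on one inference: that a repeated MANCOVA cannot use a person whose follow-up values are missing and not imputed.

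No size or direction of bias can be derived from the documents. The only relevant count is the dropout allowance of about 43 of 288, of which discontinuers are an unstated part. The 0.025 to 0.10 SD range shows what the assumed inputs imply and is not an estimate. The matter should be settled before analysis because it decides who enters the primary comparison.

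**What to change.** 1. In Eligibility criteria, remove programme discontinuation and consent withdrawal from the exclusions. Describe them as events during follow-up.
2. In Data analysis, define the primary set as all eligible persons who consented and provided T0 data. For those who withdraw, use data collected up to withdrawal where consent allows.
3. Handle discontinuers' missing T1 and T2 values by the same stated method as other missing measurements, either the planned expectation-maximization imputation or a likelihood-based model, identically in both groups.
4. Report the analysis restricted to those who completed rehabilitation as a labelled sensitivity analysis, and give the number of discontinuers by period and centre.
5. If discontinuers' data cannot be retained, drop the intention-to-treat label and name the set as those who completed rehabilitation.

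**Follow-up questionnaires.** Any sent to discontinuers must go to both groups on the same terms. This may no longer be possible for the control group at T1. If the first centre began in September 2023, with starts five months apart and four-month preparation phases, the third centre's control recruitment ended around October 2024, before publication in May 2025. Adding follow-up for the intervention group alone would create unequal follow-up.

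**Cost.** The change needs new wording, slightly more analysis work and no extra enrolment. It relies on a missing-at-random assumption for discontinuers.

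It may also dilute the effect. Suppose all 288 are analysed with the 2-degree-of-freedom test that reproduces 244, and a share q discontinue with no effect. Then f = 0.20 × (1 − q):

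| Assumed q | f | Power |
|---|---|---|
| 5% | 0.19 | 0.827 |
| 10% | 0.18 | 0.782 |
| 15% | 0.17 | 0.731 |

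If discontinuers keep half the effect, power is 0.847, 0.827 and 0.805. These figures treat imputed values as observed, so they are optimistic. The values of q are assumptions.

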#### Sample size

With the three PAHCO dimensions (i.e., movement competence, control competence, and self-regulation competence), the present study lists three main outcomes. We set *p* ≤.05 for the repeated multivariate analyses of covariance (MANCOVA) and assume a pre-post correlation (within-subjects factor) of *r* = .40, as a previous study revealed an autoregressive *r* = .418 [52]. To detect a significant intervention effect of medium magnitude (*η*^2^ = 0.04; *f* = 0.20) paired with a statistical power ≥ 80%, we must recruit a total of 244 persons undergoing rehabilitation. Given the number of rehabilitation centers (*n* = 3), we are advised to aim for 82 participants per center. Since each rehabilitation center includes persons undergoing rehabilitation at two time periods, that is, before modification (i.e., CG) and after modification (i.e., IG), we must recruit a number of *n* = 41 participants per time period in the respective rehabilitation center. Considering a longitudinal dropout rate of 15%, we aim to recruit *n* = 48 participants per time period in each rehabilitation center.

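### EM imputation of whole missing questionnaires, read naturally as one completed data set, either understates uncertainty or dilutes the group difference at the 1-year follow-up, depending on the imputed share

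*Protocol article*

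**What the plan says.** All references are to the Effectiveness study part of the Protocol article.

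- **Data analysis, missing data.** Two classes are separated. "Reasonable dropouts (e.g., discontinuation of the planned medical rehabilitation program) will be treated as structurally missing data". Everything else is filled: "other missing items and measurements will be imputed with the expectation maximization algorithm". The word measurements extends the rule from skipped items to whole questionnaires.
- **Data analysis, analysis set.** Under an intention-to-treat heading, "all persons undergoing rehabilitation meeting the eligibility criteria and initially providing consent will be included in the statistical effectiveness computations".
- **Data analysis, model.** Time is the within-subjects factor, CG/IG the between-subjects factor and centre a control variable: "We will integrate all these factors into repeated MANCOVA with the primary outcomes".
- **Sample size.** The three PAHCO dimensions are primary ("the present study lists three main outcomes"), tested at the 5% level. The total of 244 is raised for 15% longitudinal dropout to 48 per period and centre.
- **Data collection.** T0 and T1 questionnaires are handed out in the centre. T2 is posted a year after rehabilitation starts.

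The text gives no number of imputed data sets, no residual noise, no pooling rule and no list of variables in the EM model.

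**The concern.** EM imputation in its ordinary form puts one conditional-mean value in each gap. That value has no residual scatter, and nothing downstream records that it was estimated. A complete-data MANCOVA then counts it as an observation. What follows depends on whether the EM model knows a participant's group:

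- **Group included.** The effect estimate is unbiased when data are missing completely at random, but its standard error is too small and the test rejects too often.
- **Group left out.** Imputed values in both groups follow the same pooled prediction, so the IG–CG difference is pulled towards zero.

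These are alternatives and do not occur together. T2 is most exposed because it is the only postal wave and comes last. The long-term half of the effectiveness objective rests on it.

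**Working it through.** **The plan's own figures.** With noncentrality λ = f²N, f = 0.20, α = 0.05, power 80% and 2 numerator degrees of freedom (two groups, three time points), the smallest N is 243, or 244 with equal groups. This matches the plan. Then 244 / 0.85 = 287.1, which rounded up to six equal cells gives 288 = 6 × 48. The sample size is not in dispute. It shows that the plan expects 15% of participants to be lost.

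**Inputs for the check.**
- From the plan: 288 participants, two periods, three centres, three outcomes at three time points, α = 0.05, correlation over time 0.40.
- Assumed: correlation between dimensions 0.5 (varied from 0.2 to 0.7), whole T2 questionnaires missing completely at random in 5% to 40%, and a true T2 effect of 0.40 SD where power or bias is studied.
- Test: multivariate test of group on T0–T2 change in the three dimensions, adjusted for centre, with filled values treated as observed. 2,000 runs per scenario.

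**Rough analytic check, group included.** Take one outcome with a share m filled by the group mean and nothing borrowed from other waves. Filled cells have no residual, so the estimated variance falls to (1 − m)σ², while the sample is counted as n instead of (1 − m)n. The reported standard error is therefore (1 − m) times the true one, and

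type I error ≈ 2[1 − Φ(1.96(1 − m))] = 6.3%, 9.6% and 17.0% for m = 5%, 15% and 30%.

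Borrowing from T0 and T1 lowers this for a single outcome, and testing three outcomes jointly raises it.

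**Analytic check, group left out.** If the groups do not differ at T0 and T1, the T2 difference becomes (1 − m) × 0.40: 0.85 × 0.40 = 0.34 and 0.70 × 0.40 = 0.28. A T1 difference feeding the prediction would lessen the shrinkage.

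**Simulation.**

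| T2 imputed | Type I error, group in EM | Type I error, group left out | 0.40 SD estimated as, group left out | Power, group left out | Power, complete cases |
|---|---|---|---|---|---|
| 5% | 5.3% | about 5% | not run | not run | not run |
| 15% | 9.7% | about 5% | 0.34 | 82% | 84% |
| 30% | 17.6% | about 5% | 0.28 | 67% | 76% |
| 40% | 26.4% | about 5% | not run | not run | not run |

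Power with no missing data is 90%.

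- Monte Carlo standard error near 10% is √(0.1 × 0.9 / 2000) = 0.7 percentage points.
- At 5% imputed, the same runs with no missing data rejected in 4.1%, so the rise there is about one point.
- At 15%, varying the between-dimension correlation from 0.2 to 0.7 gives 9.6% to 10.2%.
- One stochastic draw in place of the conditional mean still gives 9.2% at 15% and 15.6% at 30%, so adding noise once does not cure the problem.
- A joint T0–T1–T2 test with 5% missing at T1 and 15% at T2 gives 10.8%.
- A separate simulation with slightly different correlations (2,500 runs) gave 10.3% and 18.0% at 15% and 30%.

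**After the fix.** Multiple imputation with 20 data sets, period and centre in the model, and a Rubin-type pooled multivariate test gives a type I error of 4.3% at 15% and 5.2% at 30%. The 0.40 SD effect is estimated at 0.41 in both cases, with power 89% and 81%.

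**The case against.** Four objections have weight.

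1. **Not everything missing is imputed.** A reader might take the planned 15% dropout as the imputed share. The plan does not support that: reasonable dropouts stay unimputed, and how much of the 15% they make up is not stated. So 15% is an upper end on the plan's own figure, 30% has no source in the document, and at 5% the harm is negligible. This stands. Against it, the only example of a reasonable dropout is stopping the rehabilitation programme, which does not describe someone who simply does not return a posted form.
2. **Single imputation is an inference.** The article names an algorithm, not a number of data sets. An EM-based multiple imputation with pooling would escape the criticism, and a condensed article may leave such detail elsewhere. This stands in part: one completed data set is the natural reading of what is written, but it is a reading.
3. **The short-term contrast is hardly touched.** A reader might infer that the whole primary test is unsound, or that T2 is the study's main purpose. The objectives give short- and long-term effects equal standing, and T1 is collected on site, where few gaps are to be expected. This stands.
4. **One branch is conservative.** With group left out, the bias is towards no effect and power at 15% imputed (82%) is still above the planned 80%. True, but the estimate is biased and the power lies below that of discarding the incomplete cases.

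**Conclusion.** The concern holds in a limited form. For contrasts involving T2, EM imputation of whole questionnaires followed by an ordinary MANCOVA gives either too many false positives or a diluted difference, and the article does not settle which. With group in the EM model, the nominal 5% becomes about 5% at 5% imputed, 10% at 15% and 18% at 30%. With group left out, the T2 difference loses about the imputed share.

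This rests on reading the rule as a single completed data set, on data missing completely at random, on assumed correlations between dimensions, and on an imputed share the document does not give. The documents do not support saying that the short-term result is invalid, or that the repeated MANCOVA itself must be abandoned.

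**What to change.** Reword the missing-data sentence for missing measurements. Use multiple imputation (for example 20 to 50 data sets) with group, centre and all outcomes at all time points in the imputation model. Run the planned repeated MANCOVA in each data set and pool with a Rubin-type multivariate test. Keep single EM imputation only for isolated missing items within a scale. If an EM-based multiple imputation was intended all along, stating that, with the model variables and pooling rule, is enough.

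A likelihood-based repeated-measures model using all observed time points is an acceptable alternative but is not needed to cure the defect.

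The cost is a change of wording and a little more analysis work in R. Confidence intervals become slightly wider than those from single imputation with group in the model. No new data are needed. The change should be made before the T2 data are analysed.
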